### Data collection

Data will be entered into Microsoft Excel during the course of the feasibility study, and data will be recorded only by investigators of the study. This system will help ensure compliance with medical data privacy, security and good clinical practice regulations. Data will be stored in password-protected files for 15 years and then destroyed. Physical copies of data will be kept in a locked filing cabinet. The data to be collected in this study are depicted in Table 1.

**Table 1 Tab1:** Data collection schedule and parameters to be collected

		Wk0	Wk2	Wk4	Wk6
**Patient information**	Consent and patient demographics	X			
	Medical history	X			
	Medications	X	X	X	X
	Infection risk	X			
	Immunological risk	X			
	Transplant history	X			
	Transplant course specifically documenting infection events		X	X	X
**Standard care biochemistry**	Full blood count Urea and electrolytes Fasting blood glucose HbA1c	X	X	X	X
**Uremic toxins**	Total serum IS	X			X
	Free serum IS	X			X
	Total serum pCS	X			X
	Free serum pCS	X			X
**Gut microbiota**	Bristol stool evaluation and stool sample collection	X	X		X
**Inflammatory markers**	C-reactive protein	X			X
**Quality of life (EQ-5D)**		X			X
**Prebiotic dose commencement**		X	X		
**Prebiotic dose escalation**			X		
**Gastrointestinal symptoms (GSRS)**		X	X		X
**Compliance**	Weight of powder				X
**Serious adverse events**			X	X	X
**Adverse events**			X	X	X

### Sample size

A sample size of 60 subjects will be required for an estimate of 95% confidence interval to within plus or minus 11%, assuming a recruitment rate of 80%.

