**Methods:**

Sixty kidney transplant patients will be recruited to a double-blind, placebo-controlled, randomised feasibility trial. Patients will be provided with prebiotic therapy or placebo for 4 to 6 weeks. Outcomes will include recruitment, adherence, tolerance, retention, laboratory parameters (including serum indoxyl sulphate, ρ-cresyl sulphate and stool collection), patients’ self-assessed quality of life, gastrointestinal symptoms and clinical outcomes.

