### Setting and participants

Sixty acute kidney transplant recipient patients will be recruited from the Princess Alexandra Hospital kidney transplant ward (Brisbane, Queensland, Australia) over a 6-month period. The Princess Alexandra Hospital is the only kidney transplant unit in Queensland and is the largest kidney transplant unit in the Oceania region. To be eligible to participate in this trial, participants must satisfy all of the following criteria: receive a kidney transplant at the Queensland Renal Transplant Service, be aged ≥ 18 years and be able to provide informed consent. Patients will be excluded from participation if they meet any of the following criteria: have received radiation to the bowel and/or large bowel resection, medically diagnosed and active inflammatory bowel disease, unwilling or unable to meet the requirements of the protocol and other medical, social, cultural and/or linguistic reasons negatively affecting their adherence to the protocol, at the discretion of the investigators.

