### Primary and secondary outcomes

The primary outcome of this study is feasibility of recruitment which will be defined as at least 80% of eligible subjects recruited to the study.

The secondary outcomes will include the following:Timeliness of recruitment

This will be assessed as the ability to successfully recruit 60 patients within 6 months.b)Adherence

This will be assessed as the proportion of participants adherent to prescribed study therapy (intervention or placebo) over the period of the study. Adherence will be defined as having used 80% of more of the prescribed study therapy, calculated by the % of the expected weight of the product returned divided by the initial weight of study therapy.iii)Tolerance

This will be assessed as the proportion of patients who continue the prebiotic supplementation. Tolerance will be defined as 80% of the recruited patients taking the prescribed study therapy during the study period.iv)Gastrointestinal symptom assessment

The gastrointestinal symptom assessment will be assessed as the changes in the Gastrointestinal Symptom Rating Scale score from baseline compared with the score at the time of the completion of the PREBIOTIC trial.e)Retention

This will be assessed as the proportion of patients who remain in the PREBIOTIC study for the entire study period.f)Laboratory samples

There will be two aspects to this outcome. The first part will examine the proportion of participants providing two stool samples at designated times (during the first week and between 4 and 6 weeks post-kidney transplant) with sufficient material to assess gut microbiota (stool sample analysis via shotgun metagenomic sequencing to a target depth of 3 Gbp using NovaSeq 6000, 2 × 150 base pair, paired-end chemistry). The second part of this outcome will assess the proportion of participants providing two blood samples for serum indoxyl sulphate and p-cresyl sulphate measurement at designated times (during the first week and between week 4 to week 6 post-kidney transplant).g)Quality of life

This will be assessed as the changes in the overall quality of life score (measured by EQ-5D survey) from baseline compared with the score measured at the completion of the PREBIOTIC trial.h)Infectious events

This will be assessed as the proportion of patients who develop at least one infectious event requiring hospital admission or antimicrobial therapy. Infectious adverse events of special interest would include the following:

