### Planned analysis

As this is a feasibility study, data will be analysed via descriptive statistics, expressing frequencies (percentages) for categorical data, mean ± standard deviation for continuous normally distributed data or median (interquartile range) for continuous non-normally distributed data. In addition, confidence intervals will be presented for all descriptive statistics. Outcome measures and the corresponding statistical measures are shown in Table 2. Analysis will be performed on an intention-to-treat basis. Patients discontinuing the study drug for whatever reason will be encouraged to continue follow-up in the trial. The null hypothesis will be rejected at the 0.05 level. The statistical analyses will be performed using Stata (version 14, 2016, Statacorp, College Station, TX, USA).

**Table 2 Tab2:** Outcomes and corresponding measures

Outcome	Measure
Proportion of eligible patients who agree to take part in the study	% (95% CI)
Ability to successfully recruit 60 patients within 6 months	% (95% CI)
Proportion of participants adherent to prescribed study therapy (intervention or placebo) over the period of the study	% (95% CI)
Proportion of patients who continue to the prebiotic supplementation	% (95% CI)
Mean changes in the Gastrointestinal Symptom Rating Scale	Mean change (SD)
Proportion of patients who withdraw from the PREBIOTIC study	% (95% CI)
Proportion of participants providing two stool samples at designated times (the first week and between week 4 to week 6 post-kidney transplant) to assess gut microbiota changes	% (95% CI)
Proportion of participants providing two blood samples at designated times (the first week and week 6 post-kidney transplant)	% (95% CI)
Changes in the overall quality of life (measured by EQ-5D survey)	Mean change (SD)
Proportion of patients with at least one infectious event	% (95% CI)

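### The ±11-point precision treats 60 as the denominator of the recruitment rate, but 60 is the number recruited; at 80% the denominator is about 75 eligible patients

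*Protocol article*

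**What the plan says.** The whole sample-size rationale is one sentence: "A sample size of 60 subjects will be required for an estimate of 95% confidence interval to within plus or minus 11" per cent, "assuming a recruitment rate of 80" per cent. It gives no formula and does not say whether the 60 are eligible or enrolled.

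The rate in question is the primary outcome. Primary and secondary outcomes describes it as "feasibility of recruitment which will be defined as at least 80% of eligible subjects recruited to the study". Table 2, under Planned analysis, lists it as "Proportion of eligible patients who agree to take part in the study", to be reported as a percentage with a 95% confidence interval. In both places the denominator is eligible patients.

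Elsewhere 60 is the number enrolled. The abstract says "Sixty kidney transplant patients will be recruited to a double-blind, placebo-controlled, randomised feasibility trial". Setting and participants says "Sixty acute kidney transplant recipient patients will be recruited from the Princess Alexandra Hospital kidney transplant ward". The timeliness outcome reads "This will be assessed as the ability to successfully recruit 60 patients within 6 months". Aims and objectives and the Discussion use 60 in the same sense. No section gives the number of eligible patients expected.

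**The concern.** A recruitment rate is recruits divided by eligible patients, and its precision depends on the eligible count. The article fixes the numerator at 60, yet its precision figure fits 60 as the denominator. The two uses are incompatible at any rate below 100%.

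Two things are at stake. First, this is the article's only justification for the sample size, and it concerns the primary outcome; if it is worked out on the wrong count, it does not support the target. Second, the Discussion names two aims, enrolling 60 in the 6-month window and estimating the share of eligible patients who accept. The number of eligible patients connects them, and a reader cannot judge whether both aims can be met together without it.

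**Working it through.** **Inputs.** Assumed rate p = 0.80, 60 subjects, stated half-width 11 points, and a "95% confidence interval" taken as two-sided, z = 1.96 (all from Sample size). Denominator of the rate: eligible patients (Primary and secondary outcomes; Table 2). Number recruited: 60 (abstract, Aims and objectives, Setting and participants, timeliness outcome). Recruitment period: 6 months.

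**Step 1. Reproduce the stated figure with 60 as denominator.**

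- Simple Wald, z·√(p(1−p)/n): 1.96 × √(0.16/60) = 0.1012, or ±10.1 points. Under this formula 11 points needs n = 1.96² × 0.16 / 0.11² = 50.8, so 51. This does not give 60.
- Wald with continuity correction, adding 1/(2n): 0.1012 + 1/120 = 0.1095, or ±10.95 points. At n = 59 it is 0.1021 + 1/118 = 0.1105. So 60 is the smallest n that keeps the half-width within 11 points.
- Exact (Clopper-Pearson) for 48/60, with limits at the 0.025 quantile of Beta(48, 13) and the 0.975 quantile of Beta(49, 12): 67.7% to 89.2%, half-width 10.8 points.
- Wilson: 68.2% to 88.2%, half-width 10.0 points.

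The stated 11 is therefore sound arithmetic for n = 60 under two standard methods.

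**Step 2. Find the denominator that the definitions imply.**

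- 60 recruited at 80%: 60 / 0.80 = 75 eligible, and 75 / 6 = 12.5 per month.
- 60 eligible at 80%: 60 × 0.80 = 48 recruited, 12 short of the target of 60.

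**Step 3. Recompute the precision with 75 as denominator.**

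| Method | 48/60 | 60/75 |
|---|---|---|
| Wald half-width | 10.1 | 9.1 |
| Continuity-corrected half-width | 10.95 | 9.7 |
| Wilson half-width | 10.0 | 8.9 |
| Exact 95% interval | 67.7% to 89.2% | 69.2% to 88.4% |
| Exact half-width | 10.8 | 9.6 |

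For 60/75 the exact interval runs 10.8 points below 80% and 8.4 points above it.

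**Step 4. Check the direction at other rates.** With 60 recruits at rate r, the eligible number is 60/r and the Wald half-width is 1.96 × √(r²(1−r)/60).

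| Rate | Eligible | Wald half-width |
|---|---|---|
| 60% | 100 | 9.6 |
| 70% | 85.7 | 9.7 |
| 80% | 75 | 9.1 |
| 90% | 66.7 | 7.2 |

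The maximum is at r = 2/3, where r²(1−r) = 4/27 = 0.148 and the half-width is 1.96 × √(0.148/60) = 0.097. With 60 recruits, the Wald half-width stays below 11 points at every rate.

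**The case against.** The strongest reply is that the sentence promises a bound, and the bound holds. Read with 60 as recruits and 75 as eligible, every method gives a half-width below 11 points, and the exact interval lies wholly within 11 points of 80%. This stands: the slip understates the precision that the trial would have and changes nothing in its conduct.

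A second reply is that the route to 11 is inferred, since the article shows no formula. That is fair as far as it goes. The longer, lower arm of the exact interval for 60/75 is 10.8 points and also rounds to 11. But the article states a symmetric plus or minus, and the symmetric half-width for 60/75 is 9.6. The continuity-corrected calculation at n = 60 fits the stated pair of numbers closely, with 59 just failing. On either route the sentence leaves open which count the 60 is, and the eligible number is absent.

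A third reply is that 11 points could be meant for proportions among the enrolled, such as adherence or retention, where 60 is the right denominator. The sentence itself ties the figure to the recruitment rate, so this does not rescue it as written.

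Some stronger readings are tempting and do not hold. A reader who tries only the simple Wald formula might infer a calculation error; Step 1 shows there is none at n = 60, and the exact method is not the only one that yields 11. A reader might infer that the trial is too small or will miss its stated precision; Steps 3 and 4 show the opposite. Nor does the sentence describe something the trial will not estimate: the recruitment rate is the primary outcome and Table 2 reports it with an interval. Only its denominator is misplaced.

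**Conclusion.** The point holds as a denominator error in the conservative direction. The half-width of 11 points belongs to 60 eligible patients, of whom about 48 would be recruited. For the planned 60 recruits at 80% there are about 75 eligible patients, and the half-width is about 9 to 10 points, some 1 to 1.2 points narrower within any one method. The trial is not undersized and its target need not change. What the sentence fails to do is establish that 60 recruits are required, because that precision would be reached with about 48.

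This rests on the assumed 80% rate, a two-sided 95% level, the reading of the rate as recruited over eligible that both the outcome definition and Table 2 give, and treating the eligible count as fixed at 75. The importance is modest: wrong as written, with no effect on enrolment.

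**What to change.** Restate the Sample size section, for example:

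*Recruiting 60 patients at an expected 80% requires about 75 eligible patients over 6 months (about 12.5 per month), giving a 95% CI for the recruitment rate of about 69% to 88% (exact). For proportions among the 60 randomised, an 80% estimate would have a 95% CI of about 68% to 89%.*

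This says which count the 60 is, supplies the missing eligible number, and separates the precision of the primary outcome from that of outcomes measured in enrolled patients. The cost is one reworded passage, with no change to enrolment, outcomes or analysis.

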### Planned analysis

As this is a feasibility study, data will be analysed via descriptive statistics, expressing frequencies (percentages) for categorical data, mean ± standard deviation for continuous normally distributed data or median (interquartile range) for continuous non-normally distributed data. In addition, confidence intervals will be presented for all descriptive statistics. Outcome measures and the corresponding statistical measures are shown in Table 2. Analysis will be performed on an intention-to-treat basis. Patients discontinuing the study drug for whatever reason will be encouraged to continue follow-up in the trial. The null hypothesis will be rejected at the 0.05 level. The statistical analyses will be performed using Stata (version 14, 2016, Statacorp, College Station, TX, USA).

**Table 2 Tab2:** Outcomes and corresponding measures

Outcome	Measure
Proportion of eligible patients who agree to take part in the study	% (95% CI)
Ability to successfully recruit 60 patients within 6 months	% (95% CI)
Proportion of participants adherent to prescribed study therapy (intervention or placebo) over the period of the study	% (95% CI)
Proportion of patients who continue to the prebiotic supplementation	% (95% CI)
Mean changes in the Gastrointestinal Symptom Rating Scale	Mean change (SD)
Proportion of patients who withdraw from the PREBIOTIC study	% (95% CI)
Proportion of participants providing two stool samples at designated times (the first week and between week 4 to week 6 post-kidney transplant) to assess gut microbiota changes	% (95% CI)
Proportion of participants providing two blood samples at designated times (the first week and week 6 post-kidney transplant)	% (95% CI)
Changes in the overall quality of life (measured by EQ-5D survey)	Mean change (SD)
Proportion of patients with at least one infectious event	% (95% CI)

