## Methods

### Aims and objectives

The aim of this study is to assess the feasibility of performing a randomised controlled trial of prebiotics in reducing infections and disruptive gastrointestinal symptoms in kidney transplant recipients. The primary objectives are to determine the following:This Prospective Randomised Evaluation of preBiotic In solid Organ Transplant recipients to prevent Infectious Complications (PREBIOTIC) study will be able to successfully recruit 60 patients within 6 months.Kidney transplant recipients will be adherent to prebiotic supplementation during the first 4 to 6 weeks following kidney transplantation.Prebiotic supplementation will be well tolerated by kidney transplant recipients during the first 4 to 6 weeks following kidney transplantation.Withdrawal of kidney transplant recipients will be minimal from a randomised controlled trial examining the safety and efficacy of prebiotic supplementation as an infection prevention strategy during the first 4 to 6 weeks following kidney transplantation.Kidney transplant recipients will be able to provide (in at least 80% of patients) two stool samples and two blood samples during the first 4 to 6 weeks following kidney transplantation to ascertain whether prebiotic supplementation improves dysbiosis.Prebiotic supplementation in kidney transplant recipients will result in improved quality of life during the first 4 to 6 weeks following kidney transplantation.Prebiotic supplementation in kidney transplant recipients will reduce the number of infections and infection-related hospitalisations during the first 4 to 6 weeks following kidney transplantation.

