Other outcomes which will be explored in this study include patient-centred factors such as quality of life and the patient’s symptoms with respect to their gastrointestinal health. A 6-month prospective, randomised, double-blind, placebo-controlled crossover trial of probiotic bacterial formulation involving 46 participants with stages 3 or 4 chronic kidney disease from four countries reported significant improvements in quality of life (86%, *p* < 0.05) [22]. However, there are no studies that have examined the impact of prebiotic supplementation on quality of life in patients with kidney disease. Furthermore, this feasibility study will include a gut microbiota analysis evaluating whether prebiotic strains alter the microbiota of the large bowel, as has been shown in infants [23] and influence serum concentrations of the putative uraemic toxins, indoxyl sulphate and serum *ρ*-cresyl sulphate [24].

The use of green banana-resistant starch in this feasibility study is a promising nutritional intervention since the functional properties may enhance short chain fatty acid production without triggering irritable bowel syndrome symptoms, which fermentable oligosaccharides, disaccharides, monosaccharides and polyols (FODMAPS) are known to do [25, 26]. Short-chain fatty acids, primarily acetate, propionate and butyrate are known to lower intestinal pH, which in turn can inhibit the growth of pathogenic bacteria [27, 28] and promote favourable metabolic effects leading to a reduction in the incidence of metabolic syndrome and improved insulin sensitivity [29, 30].

In summary, this PREBIOTIC study aims to provide proof-of-concept data to elucidate whether altering the gastrointestinal microbiota in the kidney transplant population is likely to be effective, tolerable and prevent infectious complications. If this feasibility study is shown to be successful, it will be used to inform the design and conduct of a large scale, multicentre randomised controlled trial.

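### The analysis section plans description only, then rejects an unnamed null hypothesis at 0.05; two efficacy claims are called primary objectives, but the listed measures contain no prebiotic-versus-placebo contrast.

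*Protocol article*

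**What the plan says.** Four parts of the protocol article bear on this.

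- **Aims and objectives.** The overall aim is the feasibility of a randomised trial. The list of seven items is introduced with "The primary objectives are to determine the following". Two of the seven are directional effect claims: "Prebiotic supplementation in kidney transplant recipients will result in improved quality of life" and "Prebiotic supplementation in kidney transplant recipients will reduce the number of infections and infection-related hospitalisations".
- **Primary and secondary outcomes.** One primary outcome is named: "The primary outcome of this study is feasibility of recruitment which will be defined as at least 80% of eligible subjects recruited to the study". Quality of life (EQ-5D), the Gastrointestinal Symptom Rating Scale (GSRS) and infectious events are secondary.
- **Sample size.** N = 60 gives a 95% confidence interval of ±11 points around an assumed recruitment rate of 80%. No between-arm effect, SD or power is given.
- **Planned analysis.** Analysis is descriptive and by intention to treat, and "In addition, confidence intervals will be presented for all descriptive statistics". The section then states: "The null hypothesis will be rejected at the 0.05 level". In Table 2 the row "Mean changes in the Gastrointestinal Symptom Rating Scale" and the EQ-5D row have the measure mean change (SD), and the infection row has a percentage with 95% CI. No row gives a difference, ratio or test between prebiotic and placebo.

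The Discussion adds that the study should give proof-of-concept data on whether altering the microbiota "is likely to be effective, tolerable and prevent infectious complications".

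**The concern.** Two statements in one paragraph cannot both be followed. A purely descriptive analysis has no null hypothesis to reject. A rejection rule at 0.05 needs a hypothesis, an endpoint and a test, and the article names none. This is a conflict in the text, not detail left to a statistical analysis plan.

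The objectives add to it. Two items with primary status assert that the prebiotic has an effect, but the outcome section does not make them primary and the sample size does not support testing them. Nor do the listed measures address them. For quality of life, and for GSRS, which serves the overall aim on gastrointestinal symptoms, the measure is change from baseline. Participants usually consent and start between day 5 and day 12 after transplant, so change over the next 4 to 6 weeks includes recovery from surgery in both arms. Only the contrast with placebo can separate that recovery from any effect of the prebiotic.

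Two misreadings are at stake. A before-after improvement could be reported as a prebiotic effect. Or tests could be chosen after the fact under a general 0.05 rule, in a trial where a null result says little and an isolated positive one is easily over-read.

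**Working it through.** **1. The plan's own figure.** Inputs from Sample size: n = 60, p = 0.80.

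- Plain Wald half-width: 1.96 × √(0.80 × 0.20 / 60) = 0.101.
- With continuity correction: 0.101 + 1/(2 × 60) = 0.110.
- Exact (Clopper-Pearson) interval for 48/60: 0.677 to 0.892, mean half-width 0.108.

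The stated ±11 points is reproduced by the corrected or exact interval. It concerns one proportion and carries no information about a comparison of arms.

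**2. The passages side by side.**

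| Item | Aims and objectives | Outcomes | Table 2 measure |
|---|---|---|---|
| Recruitment of eligible patients | Feasibility aim; listed item is 60 in 6 months | Primary | % (95% CI) |
| Quality of life | Primary objective, directional | Secondary | Mean change (SD) |
| Infections | Primary objective, directional | Secondary | % (95% CI) |
| GSRS | In the overall aim only | Secondary | Mean change (SD) |

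None of these measures contrasts the arms, and the 0.05 rule is attached to none of them.

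**3. What a 0.05 test could do, for scale only.** Allocation is 1:1 (Randomisation), so 30 per arm if 60 are randomised. The Background gives infection in 40% to 65% of recipients, without a time window. Using that range as the 4 to 6 week control risk is an assumption, and so is the halving.

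Normal approximation, two-sided 0.05: power = Φ[(p1 − p2 − 1.96 × s0) / s1], with s0 = √(2 × p̄(1 − p̄)/30), s1 = √((p1(1 − p1) + p2(1 − p2))/30) and p̄ the mean of p1 and p2.

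- 40% v 20%: s0 = 0.1183, s1 = 0.1155; (0.20 − 0.2319)/0.1155 = −0.276; power 0.39. Fisher's exact test: 0.30.
- 65% v 32.5%: s0 = 0.1291, s1 = 0.1220; (0.325 − 0.2530)/0.1220 = 0.590; power 0.72. Fisher: 0.64.
- If the risk were only 20% (a further assumption), 20% v 10%: power 0.19. Fisher: about 0.10.

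Half-width of the 95% CI for the risk difference, 1.96 × s1:

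- 40% v 20%: 1.96 × 0.1155 = 0.226.
- 65% v 32.5%: 1.96 × 0.1220 = 0.239.
- Equal risks of 40%, 50% and 65%: 0.248, 0.253 and 0.241.

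So the half-width is about 23 to 25 points across the assumed range. For a continuous outcome, 30 per arm gives 80% power only for a difference of about 0.72 SD.

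**The case against.** The strongest reply is that this is a feasibility trial. Its aim, primary outcome and sample size all concern feasibility, and describing clinical outcomes without testing efficacy is proper for that purpose. The by-arm layout, contrast and covariates could also be in an analysis plan that is not shown. Much of this stands, and it rules out several stronger readings.

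- A reader might infer that the trial leaves its main question unanswered. It does not: the declared question is feasibility, and Table 2 has measures for it. The gap concerns the efficacy objectives.
- A reader might infer that the Table 2 rows pool the arms. The table does not say so. The design is placebo-controlled and the analysis is by intention to treat, so by-arm reporting may be intended.
- A reader might infer that the main trial will have no SDs or event rates to draw on. Table 2 does supply SDs and an infection percentage; only the between-arm effect is unlisted.
- A reader might infer that GSRS and EQ-5D will lack confidence intervals because their rows show only an SD. The text promises intervals for every descriptive statistic, so this is incomplete shorthand.
- A reader might infer from the Discussion that effectiveness is part of a rule for proceeding. No such rule is stated; the article says only that a successful feasibility study will inform the larger trial.

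The reply does not remove the conflict within Planned analysis, or the one between the objectives and the outcomes. An analysis plan can add detail, but it cannot follow both statements.

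**Conclusion.** The point holds, as something that should be fixed. Planned analysis contradicts itself on whether anything is tested. Aims and objectives gives primary status to two effect claims that the outcome section makes secondary. The measures listed for those claims contain no contrast with placebo and so cannot address them.

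The consequence lies in interpretation. Primary outcome, sample size, randomisation and data collection are unaffected. The power figures (about 30% to 72% for a halving of infection) and the interval of about ±23 to ±25 points show only that N = 60 was not built for such a test. They rest on an assumed 4 to 6 week control risk of 40% to 65%, an assumed halving and 30 analysed per arm. Power falls if the risk in that window is lower. The textual contradictions do not depend on any of these assumptions.

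**What to change.** 1. In Planned analysis, delete the sentence on rejecting a null hypothesis. If a test is kept, state its hypothesis, endpoint, method and sidedness, and label it exploratory.
2. In Aims and objectives, relabel the quality-of-life and infection items as secondary or exploratory, in line with the outcome section.
3. In Table 2, report GSRS and EQ-5D by arm, with the between-arm difference and 95% CI from a model adjusted for baseline score and the stratification factors (age group, sex). Report infection by arm, with the risk difference and 95% CI. State that no efficacy conclusion will be drawn from these estimates.

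The cost is wording in the protocol and any analysis plan. Baseline GSRS and EQ-5D are already collected at week 0 (Table 1), and age group and sex are known at randomisation. No extra patients, visits or measurements are needed. The change should be made before any unblinded analysis.
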